### Patient and Public Involvement

No patients or public were involved in the design of this study.

**Figure 1 figure1:**
[figure not shown]
Design of the FBB-CT01 device (415 nm and 450 nm). The patient lies on the treatment table and receives treatment from the light engine above.

### Statistical Considerations

The primary analysis will be performed based on the full analysis set following the intention-to-treat principle. Dropouts during first 4 weeks of treatment will be replaced. Patients missing more than 5 irradiation appointments in total until day 25 (inclusive) or more than 3 consecutive irradiation appointments until day 25 (inclusive) will be considered dropouts and will be replaced. Dropouts after day 25 of the study protocol will not be replaced and will be analyzed in the intention-to-treat population. Sensitivity analysis will be done on the per-protocol population. The difference between the end of treatment after 8 weeks and baseline in primary effectiveness endpoint EASI will be analyzed using pairwise 2-sample *t* tests between each of both active treatments against placebo. As sensitivity analysis, an analysis of covariance will be used with study site, gender, and the hand out of topical emollient as additional factors and the EASI baseline value, age, and Fitzpatrick skin type as covariates. Other continuous secondary endpoints will be analyzed analogously. The EASI response will be analyzed primarily using chi-square test and as a sensitivity analysis with logistic regression. Time until treatment response will be analyzed using Kaplan-Meier estimator and log-rank test. In a further sensitivity analysis, if both wavelengths show better effectiveness than placebo, a pooled comparison against placebo will be done to increase the sample size.

The two comparisons, namely, 415 nm versus placebo and 450 nm versus placebo will be evaluated equally. To address the multiplicity, a success will be declared if both comparisons are statistically significant at an alpha level of .05 or if one of these two is statistically significant with respect to half of alpha at .025.

The two risk differences between one of each blue light irradiation treatments against placebo of the rates of patients with at least one device-related adverse event (rated as possible, probable, or certain) will be compared using asymptotic Wald test of noninferiority for the risk difference. Missing values for the primary and secondary endpoints will be replaced using proper single regression methods (IVEware; University of Michigan, Ann Arbor, MI). Besides the scores (such as EASI scores), the study site, study visits with the documented EASI score, treatment group, gender, age, hand out of topical emollient, and Fitzpatrick skin type will be included in the regression models. In safety analysis, per-protocol analysis, and explorative analysis, missing values will not be replaced.

After the completion of the treatment phase of about 75 patients, first, the EASI score difference between the end of treatment and baseline and, second, the rates of device-related AEs will be analyzed descriptively using *t* test and Fisher’s exact test, as appropriate (interim analysis). Based on the estimates, it will be evaluated whether a total of 150 patients will be sufficient to show superiority against placebo at the end of the study.

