### Study Population

A total of 150 patients with atopic dermatitis will be recruited at 3 sites: Geneva, Marburg, and Göttingen. The recruitment will be independent of the severity of disease and is limited to 50.0% (75/150) at each site. A sample size of 50 patients per group will have 84% power to detect a mean effect size of 0.6.

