### Methodology

We will randomize 150 patients diagnosed with atopic dermatitis 1:1:1 to arm 1 (irradiation for 30 minutes at 415 nm wavelength), arm 2 (irradiation for 30 minutes at 450 nm wavelength), and arm 3 (irradiation for 30 minutes at low-dose, placebo). We will stratify randomization by study site and initial EASI score (assessed during screening visit) with permuted and variable block sizes. For each strata combination, a list of separate randomization sequences will be generated using SAS 9.3 (Cary, NC). Irradiation will be scheduled 3 times a week for 8 weeks. Participants will be followed up for 4 weeks after the last irradiation. Patients will be blinded by wearing tinted protective goggles that disenable the distinction of different wavelengths of light. Medical doctors will examine patients in rooms other than those equipped with the investigational medical devices. These examiners are blinded and are, therefore, not involved in the preparation and process of irradiation. If the safety of an enrolled patient is potentially jeopardized, the investigator can break the blinding of the treatment. According to the predefined study schedule, we will measure skin pigmentation with a mexameter; take photos and blood samples; measure blood pressure; and gather data on Fitzpatrick skin type, DLQI, itch on visual analog scale, SCORAD, IGA, EASI, and PO-SCORAD scores. Detailed information on assessments is depicted in the study schedule (Multimedia Appendix 2). If the EASI score increases by 50% or more compared to baseline after at least 4 weeks of treatment (earliest: day 28=visit 13), a rescue scheme can be applied that allows the use of topical steroids or antihistamines. The investigator will decide whether to prescribe these medications, in what doses, and for how long. The respective patient will not drop out, but the rescue medication as well as the day of rescue will be documented. The study database will be provided by the Universitätsmedizin Göttingen, Ressort Forschung und Lehre, Referat Klinisches Studien Management using secuTrial, which is a browser-based electronic data capture system compliant with Good Clinical Practice (audit trail, role-rights concept). The database will be accessible via the internet.

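### The primary analysis is called intention-to-treat, but the replacement rule appears to leave early dropouts and poor attenders (to day 25) out of it

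*Protocol article*

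**What the plan says.** All the relevant sentences stand together in the protocol article under Statistical Considerations.

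- The population is named first: "The primary analysis will be performed based on the full analysis set following the intention-to-treat principle".
- Replacement follows: "Dropouts during first 4 weeks of treatment will be replaced".
- An attendance rule then widens the meaning of dropout. Up to and including day 25, anyone who misses more than 5 irradiation appointments in total, or more than 3 in succession, "will be considered dropouts and will be replaced".
- Later losses are treated differently: "Dropouts after day 25 of the study protocol will not be replaced and will be analyzed in the intention-to-treat population".
- The only other efficacy population named is a restricted one: "Sensitivity analysis will be done on the per-protocol population".

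No sentence says in which efficacy set, if any, a replaced patient is analysed. Elsewhere, Methodology states "We will randomize 150 patients diagnosed with atopic dermatitis 1:1:1", and Study Population states "A sample size of 50 patients per group will have 84% power to detect a mean effect size of 0.6".

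**The concern.** Intention-to-treat means that every randomised patient is compared in the assigned arm. The sentence on later dropouts gives them two features: they are not replaced, and they are analysed. If early dropouts were also analysed, the second feature would distinguish nothing. The natural reading is therefore that early dropouts and poor attenders are taken out and others enrolled in their place.

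The attendance rule is a compliance criterion of the kind that normally defines a per-protocol set. It can catch a patient who is still attending and whose week-8 EASI could be measured. A replacement restores the number analysed but does not restore the comparison between randomised groups.

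Early leaving may differ by arm. Investigational Devices gives the active devices 40 mW/cm² with fans and the placebo device 0.2 mW/cm² without fans. Safety and Risk to Benefit Rationale lists thermal discomfort as foreseeable. If leaving does differ, the primary test compares those who stayed through about four weeks, and randomisation no longer guarantees its error rate. The per-protocol sensitivity analysis cannot reveal this, because it restricts the set further.

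**Working it through.** **The plan's own figure.** Inputs from Study Population: 50 per group, standardised effect 0.6. A two-sample t test at two-sided 0.05 gives power 0.844; the normal approximation gives 0.851. The stated 84% is reproduced, with no allowance for dropout. The sample size is not in dispute, and two-sided 0.05 is used below because it matches the plan's figure (sidedness is not stated).

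**What the attendance rule catches.** Methodology schedules 3 irradiations a week, so about 3 × 4 = 12 fall in the first four weeks. Missing more than 5 means missing at least 6 of about 12, or half. Such a patient has not necessarily left the trial.

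**How many could fall outside the primary set.** The dropout rate d is not given; 5% to 20% is assumed. If 150 retained patients are reached by replacement, the number randomised is 150/(1 − d).

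| d | Randomised | Outside the primary set |
|---|---|---|
| 5% | 158 | 8 |
| 10% | 167 | 17 |
| 15% | 177 | 27 |
| 20% | 188 | 38 |

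**Possible shift in the effect.** Let a share dA of the active arm and dP of placebo be excluded, and let excluded patients do k SD worse than retained ones in both arms. The mean of a randomised arm is then worse than its retained mean by d × k. With no true difference between the randomised arms, the retained-set difference in favour of light is (dA − dP) × k.

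Assume dA = 15% and dP = 5%:

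- k = 0.5: 0.10 × 0.5 = 0.05 SD, which is 0.05/0.6 = 8% of the planned effect.
- k = 1.0: 0.10 × 1.0 = 0.10 SD, which is 0.10/0.6 = 17% of the planned effect.

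**Effect on the error rate.** With 50 retained per arm, SE = √(2/50) = 0.20 SD. The two-sided rejection rate is Φ(λ − 1.96) + Φ(−λ − 1.96), with λ = shift/0.20.

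- Shift 0.05: λ = 0.25, rate about 5.7%.
- Shift 0.10: λ = 0.50, rate about 7.9%.
- dA = dP = 10% with the same k in both arms: shift 0, rate 5.0%.
- dA = 5%, dP = 15%: the same sizes, with the shift against light.

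**Power if everyone is analysed.** Assume early dropouts gain no benefit, so the effect is 0.6(1 − d), with n per arm 50/(1 − d). The noncentrality is 0.6(1 − d) × √(25/(1 − d)) = 3√(1 − d), and power is Φ(3√(1 − d) − 1.96). This gives about 83%, 81%, 79% and 77% for d = 5%, 10%, 15% and 20%, against 85% at d = 0.

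**The case against.** The strongest reply is that the exclusion is inferred. Replacement can be purely a recruitment rule under which an extra patient is enrolled and nobody is removed. The plan imputes missing primary endpoint values, so an early dropout could be kept, and an article may leave the exact definition of the full analysis set to the full protocol. It is true that no sentence states the exclusion outright. But the article does state the replacement rule, with thresholds, and its contrast between early and late dropouts, together with a fixed total of 150, points to exclusion. Even on the kinder reading, the text does not let a reader verify the intention-to-treat label.

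Three stronger readings are tempting and are not supported:

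- **That early leaving does depend on the arm.** There are no dropout data by arm. Adverse effects are expected to be very mild, the earlier full-body study reported only mild transitory events, and patients wear tinted goggles. The documents support only that leaving may differ.
- **That the primary result is therefore biased in favour of light.** What is lost is the guarantee from randomisation. Actual bias needs unequal rates or reasons, and it could run either way.
- **That replaced patients also vanish from the adverse event rates.** Nothing says so, and Safety and Risk to Benefit Rationale has all adverse events recorded.

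**Conclusion.** The point stands as a contradiction between the stated intention-to-treat principle and a replacement rule that, read naturally, removes patients from the primary set for what they did after randomisation. It matters because it decides whose data enter the primary test.

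Its size cannot be computed from the documents. The shift of 0.05 to 0.10 SD, and the rise from 5% to about 5.7% to 7.9%, rest on an assumed 10-point difference in early exclusion and an assumed outcome gap of 0.5 to 1.0 SD. The shift is zero when rates and reasons are equal. The finding rests on the wording, and the figures only show that a moderate imbalance would be enough to matter.

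**What to change.** - Define the full analysis set as all randomised patients in their assigned arm, including those who were replaced, regardless of missed irradiations or time of leaving.
- Use the day-25 attendance rule only to define the per-protocol set.
- Count replacements as additional randomised patients, and report the number randomised and the number replaced by arm.
- Use week-8 EASI for early dropouts and poor attenders where it was obtained; otherwise handle it with the planned missing-data method.

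**Cost.** The definition itself is a change of wording. The Results section says that enrolment closed in May 2018 and analysis is underway, so week-8 values that were never collected may not be recoverable and more values would be imputed. The effect would be somewhat diluted, with power in the 83% to 77% range derived above.

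### The primary t test on EASI change is valid but uses neither the stratification factors nor baseline EASI; adjusting for site and baseline EASI would add about 1 to 9 points of power without new data

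*Protocol article*

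**What the plan says.** Statistical Considerations fixes the primary analysis: "The difference between the end of treatment after 8 weeks and baseline in primary effectiveness endpoint EASI will be analyzed" by pairwise two-sample t "tests between each of both active treatments against placebo". No stratification factor or covariate enters this test.

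Methodology says of allocation: "We will stratify randomization by study site and initial EASI score (assessed during screening visit) with permuted and variable block sizes".

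Adjustment appears one step down, in Statistical Considerations: "As sensitivity analysis, an analysis of covariance will be used with study site, gender, and the hand out of topical emollient as additional factors", with "the EASI baseline value, age, and Fitzpatrick skin type as covariates". The article gives no reason for ranking the unadjusted test first.

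Study Population sizes the trial for a plain two-group comparison: "A sample size of 50 patients per group will have 84% power to detect a mean effect size of 0.6". On the case mix it says: "The recruitment will be independent of the severity of disease".

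**The concern.** Two separate losses follow from this choice.

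- **Baseline variance stays in the error term.** A change score removes baseline fully only if the slope of week-8 EASI on baseline EASI is 1. With any other slope, change remains correlated with baseline, and the t test counts that variation as noise.
- **The balance from stratification is not credited.** Stratifying by site and screening EASI makes the arms more alike on these factors, so the difference in means varies less from trial to trial. The t test's standard error is built from the full within-arm variance, as if allocation had been simple. It is therefore too large, and the test rejects less often than its nominal level.

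At stake is precision in the test that decides success. This matters most at .025, the level that applies when only one wavelength works.

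**Working it through.** **Inputs from the article:** 50 patients per arm, 1:1:1, effect size 0.6, 84% power; success if both comparisons reach .05 or one reaches .025; stratification by site and screening EASI.

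**Assumptions, not in the article:** two-sided tests; 0.6 is in units of the SD of the change score; the correlation r between baseline and week-8 EASI; the ratio k = SD(week 8)/SD(baseline); two EASI strata at each of the three sites.

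**Step 1: the plan's own figure.** For the two-sample t test, df = 98 and the noncentrality is 0.6 × √(50/2) = 3.0. Power is 84.4% at two-sided .05, which reproduces the stated 84%. At two-sided .025 it is 76.4%. Both figures assume simple randomisation.

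**Step 2: residual variance after adjusting for baseline.** With baseline variance s²:

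- Var(change) = s²(1 + k² − 2rk)
- Var(ANCOVA residual) = s²k²(1 − r²)
- ratio = k²(1 − r²)/(1 + k² − 2rk), which is (1 + r)/2 when k = 1

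For k = 1 and r = 0.3 / 0.5 / 0.7 / 0.9 the ratio is 0.65 / 0.75 / 0.85 / 0.95. Using d = 0.6/√ratio in the noncentral t gives adjusted power of 95.8 / 92.9 / 89.7 / 86.2% at .05 and 92.4 / 88.1 / 83.4 / 78.7% at .025.

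**Step 3: the fair comparison under stratified randomisation.** The unadjusted test also gains from stratification, so the figures in Step 1 are not its true starting point. The design was therefore simulated: 150 patients, 3 sites × 2 EASI strata, blocks of 3 or 6, k = 1 and no site effect. The t test on change was set against ANCOVA on baseline EASI and site.

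| r | t test, .05 | ANCOVA, .05 | t test, .025 | ANCOVA, .025 |
|---|---|---|---|---|
| 0.3 | 87% | 96% | 78% | 92% |
| 0.5 | 86% | 92% | 78% | 88% |
| 0.7 | 85% | 90% | 77% | 83% |
| 0.9 | 85% | 86% | 78% | 80% |

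The gain is 9 / 6 / 5 / 1 points at .05 and 14 / 10 / 6 / 2 points at .025. The simulated ANCOVA powers agree with Step 2 to within about one point or a little more, which is the order of the simulation error. The smallest gains, at r = 0.9, should be read with that in mind.

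Under the null, the t test rejected in about 2.7-4.5% of trials at nominal 5%, and ANCOVA in about 5%.

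**Step 4: other SD ratios.** The formula in Step 2, for r = 0.3 / 0.5 / 0.7, gives:

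- k = 0.8: ratio 0.502 / 0.571 / 0.628, adjusted power at .05 of 98.7 / 97.6 / 96.3%
- k = 1.2: ratio 0.762 / 0.871 / 0.966, adjusted power at .05 of 92.6 / 88.9 / 85.6%

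So the gain is larger if EASI is less spread out at week 8 than at baseline, and smaller if it is more spread out.

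**The case against.** The best defence is that this is a choice about efficiency and not an error. The test is valid, it errs on the conservative side, and the sample size was computed for this same test and is correct for it. All of that stands. A reader might infer that the trial is underpowered, that its 84% is wrong, or that the primary result would be biased. The documents support none of these.

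A second objection concerns size, and it also stands. Dividing 50 by the Step 2 ratios gives 77 / 67 / 59 patients per arm for r = 0.3 / 0.5 / 0.7, and it is tempting to say the trial gives these up. But that sum compares ANCOVA with a t test under simple randomisation, whereas this trial stratifies on EASI. Under simulated stratified allocation, the true variance of the ANCOVA estimate relative to the unadjusted one was 0.84 / 0.90 / 0.94. In precision of the estimate that is worth 50/0.84 = 59.5, 50/0.90 = 55.6 and 50/0.94 = 53.2 per arm. The rest of the power difference comes from the t test's oversized standard error. Nor do the documents show that baseline EASI will vary widely. Study Population says only that recruitment does not depend on severity.

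Third, it is tempting to say that the sponsor need only swap two analyses already planned. That is not so. The planned ANCOVA also contains gender, age, Fitzpatrick skin type and emollient hand-out. Under Inclusion and Exclusion Criteria, emollient is handed out on request during the trial, so it can respond to treatment. A model limited to treatment, site and baseline EASI is not in the article.

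Fourth, the article's Results section reports enrolment complete and analysis underway, so the timing of any change matters.

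What the defence does not supply is a reason to stratify on two factors and then leave both out of the deciding test.

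**Conclusion.** The point holds as a modest loss of efficiency, stated in the plan and not left open. The unadjusted t test is valid and conservative, and its stated power is correct. Adjusting for site and baseline EASI would restore the nominal type I error and add about 1 to 9 points of power at two-sided .05, or about 2 to 14 points at .025. These figures assume r from 0.3 to 0.9, equal SDs, two EASI strata per site, no site effect and an effect of 0.6 SD of change. The documents give neither r nor the SD ratio, so the actual gain is unknown. It could be near zero if r is very high, or above the range shown if the week-8 SD is below the baseline SD. The chi-square test for EASI response and the log-rank test for time to response are unstratified too. They concern secondary endpoints, and a logistic regression is already planned as a sensitivity analysis for response, so this is a minor matter.

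**What to change.** Make the primary analysis for both pairwise comparisons an ANCOVA on EASI change with pre-randomisation terms only: treatment, site, and baseline EASI or the screening EASI stratum. Keep the two-sample t test as the sensitivity analysis. Do not promote the planned sensitivity ANCOVA as it stands, and leave emollient hand-out out of the primary model.

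Document the change, with its reason, before unblinding. If unblinding has already happened, keep the t test primary and report the adjusted analysis beside it, labelled as such.

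Optionally, use a stratified (Cochran-Mantel-Haenszel) or adjusted test for EASI response and a stratified log-rank test for time to response.

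The cost is a few degrees of freedom (one for baseline EASI, two for three sites) and a documented amendment. No new data are needed.

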### Inclusion and Exclusion Criteria

Patients aged 18-75 years with atopic dermatitis according to the UK criteria of atopic dermatitis [14] and a body mass index between 18 and 35 kg/m^2^ who are willing to abstain from excessive sun or UV exposure and have given written informed consent will be eligible. Patients with a severe past or present disease that may affect the outcome of the study, including HIV or hepatitis B or C; patients with a risk of noncompliance with study procedures; pregnant or nursing women; patients with alcohol or drug abuse within 12 months prior to screening; patients with photodermatosis, photosensitivity, immunodeficiency, or genetic deficiencies with increased sensitivity to light; and patients who have been diagnosed with invasive skin cancer at any time or with severe actinic damage present at baseline visit will be excluded from the trial.

We will prohibit the following concomitant medication within a certain timeframe before and during the study: systemic immunosuppression treatment such as glucocorticoids, cyclosporine, azathioprine, and mycophenolate mofetil (within 8 weeks prior to baseline visit); UV irradiation treatment (within 4 weeks prior to baseline visit); topical steroids or calcineurin inhibitors (within 2 weeks prior to baseline visit); and photosensitizing medication and colors on the patient’s skin (within 3 days prior to baseline visit). Active agent-free lipid balancing creams (Unguentum leniens) will be allowed during the trial and handed out on request.

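### The sensitivity ANCOVA adjusts for emollient handed out on request during the trial, a variable that treatment may affect, so it can depart from the randomised effect in either direction

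*Protocol article*

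**What the plan says.** All references are to the protocol article.

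- **Inclusion and Exclusion Criteria**: lipid balancing creams without active agent "will be allowed during the trial and handed out on request".
- **Statistical Considerations, primary analysis**: the EASI change from baseline to week 8 is compared by "pairwise 2-sample *t* tests between each of both active treatments against placebo", without covariates.
- **Statistical Considerations, sensitivity analysis**: "As sensitivity analysis, an analysis of covariance will be used with study site" and further terms. The factors are "study site, gender, and the hand out of topical emollient as additional factors"; the covariates are baseline EASI, age and Fitzpatrick skin type.
- **Statistical Considerations, secondary endpoints**: "Other continuous secondary endpoints will be analyzed analogously".
- **Statistical Considerations, missing values**: the variable appears again as an imputation predictor: "treatment group, gender, age, hand out of topical emollient, and Fitzpatrick skin type will be included in the regression models".

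Nothing in the article limits the emollient factor to hand-out before randomisation.

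**The concern.** Every other term in the ANCOVA is fixed before treatment starts. Emollient hand-out is initiated by the patient and can happen at any time in the treatment phase.

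The article itself gives reasons why requests might depend on arm:

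- The Background section describes dry, itchy lesions and names active agent-free creams as the start of stepwise care. A request may therefore follow the symptoms that the light is meant to relieve, and the cream may itself affect EASI.
- Topical steroids and calcineurin inhibitors are prohibited, and rescue can apply only from day 28 after an EASI increase of at least 50%. A patient who is not improving has reason to ask for the cream.
- Under Investigational Devices, the active devices deliver 40 mW/cm² with fans and the placebo device 0.2 mW/cm² without. Thermal discomfort is a foreseen event. This is a second possible route from arm to requests, and it could run the other way.

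A variable that treatment affects and that also relates to outcome is a mediator, a collider, or both. Conditioning on it changes what the treatment coefficient estimates. Agreement or disagreement with the t test would then say little about the robustness of the primary result. The link may be closest for endpoints that score itch directly: the itch scale, SCORAD and PO-SCORAD.

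**Working it through.** **Inputs from the article.** 50 patients per group, effect size 0.6 and 84% power (Study Population); 1:1:1 allocation (Methodology); emollient on request and as an ANCOVA factor (as quoted above). Request rates, and how requesters differ in outcome, are not given, so those inputs are assumptions.

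**The plan's own figure.** With 50 per group, effect 0.6 and two-sided alpha 0.05 (two-sided is assumed), the noncentral t with 98 degrees of freedom gives 84.4% power and the normal approximation 85.1%. The stated 84% is reproduced. It refers to the unadjusted comparison and does not involve emollient.

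**Shift caused by the term.** Take the EASI change in SD units, negative meaning improvement. Let p be the proportion requesting cream and γ the within-arm difference in outcome between requesters and non-requesters. For a linear model with arm and request:

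adjusted effect − unadjusted effect = γ × (p_placebo − p_active)

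With the other covariates in the model, γ is conditional on them and may differ from the raw gap.

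- Requests 60% on placebo and 40% on active, requesters 0.5 SD worse: 0.5 × 0.20 = +0.10 SD. That is 0.10 / 0.6, one sixth of the planned effect.
- Low end: 0.3 × 0.10 = 0.03 SD.
- High end: 0.8 × 0.30 = 0.24 SD.

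**Simulation of the mechanism.** 400,000 patients; within-arm outcome SD of 1 before any cream effect; direct treatment effect −0.6 unless noted. A latent disease course contributes 0.5 SD to the outcome. Requests follow a probit model in arm and course.

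| Setting (assumed) | Requests, active / placebo | Unadjusted | Adjusted | Shift |
|---|---|---|---|---|
| Requests unrelated to arm | 50% / 50% | −0.60 | −0.60 | 0 |
| Related to arm, not to outcome | 31% / 50% | −0.61 | −0.61 | 0 |
| Fewer on active, requesters have worse course | 34% / 50% | −0.61 | −0.53 | +0.07 |
| Same, stronger dependence | 24% / 50% | −0.60 | −0.45 | +0.15 |
| Cream lowers EASI by 0.3 SD, no link to course | 31% / 50% | −0.54 | −0.60 | −0.06 |
| Cream effect and worse course together | 34% / 50% | −0.56 | −0.53 | +0.03 |
| No treatment effect, fewer requests on active | 34% / 50% | 0.00 | +0.07 | +0.07 |
| No treatment effect, more requests on active | 66% / 50% | 0.00 | −0.08 | −0.07 |

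Shifts were taken before rounding.

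The table shows three things. The shift vanishes unless requests depend on arm and also relate to outcome. When both hold, it can go either way, and a true null can show an effect of about 0.07 SD in either direction. If placebo patients ask for more cream and the cream helps, adjustment enlarges the estimate: the total effect is −0.6 + (−0.3) × (0.31 − 0.50) = −0.54, and the adjusted value is −0.60.

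**The case against.** **Bias is conditional, not established.** A reader might infer that the adjusted effect is biased. The article does not support that. It gives no request rates, and patients and examiners are blinded, so unequal requests would need a real treatment effect on symptoms or skin, or a failure of blinding. This stands: the point is that the estimate can be biased.

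**Some hand-out may precede randomisation.** There is a screening week, and topical anti-inflammatory treatment must have stopped within the 2 weeks before baseline. The coding of the variable is not given, and the schedule of assessments is not shown. This lowers certainty, but permission for the whole trial includes the treatment phase.

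**The primary conclusion does not rest on this model.** A reader might take the point as a threat to the primary result. It is not one: the t test has no emollient term, and the success rule ("a success will be declared if both comparisons are statistically significant at an alpha level of .05", or one at .025) is stated for the two comparisons with placebo, which the t tests make. The sentence on secondary endpoints is most naturally read as t test first and ANCOVA as sensitivity analysis, so only their sensitivity analyses are touched. Covariates of the logistic model for EASI response are not listed, so nothing can be said against it.

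**Adjustment need not dilute the effect.** This also stands; the direction depends on why patients ask and on what the cream does.

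**The illustrated shift may be small.** The central 0.10 SD is half the standard error of an unadjusted comparison, √(2/50) = 0.20 SD. That is fair as to scale. But the shift is systematic, and it separates two analyses of the same patients, which is exactly the comparison a sensitivity analysis is read for.

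**Use in the imputation models** might seem to be the same fault. It is not: a post-baseline variable is acceptable there as an auxiliary predictor.

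**Conclusion.** The point holds as a fault in a stated sensitivity model. The ANCOVA conditions on a variable that arises during the trial and that treatment may plausibly affect. If requests differ by arm and relate to outcome given the other covariates, the model does not estimate the total randomised effect and cannot serve as a robustness check on the t test. Size and direction are unknown. The 0.03 to 0.24 SD range, 5% to 40% of the planned 0.6 (0.03/0.6 and 0.24/0.6), rests wholly on the assumed request differences and outcome gaps. The fault reaches the sensitivity analyses of EASI and of the continuous secondary endpoints, and no further. It is worth correcting, but it ranks below a flaw in the primary analysis.

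**What to change.** Restrict the sensitivity ANCOVA to pre-randomisation variables: site, baseline value of the outcome being analysed, age, gender and Fitzpatrick skin type. Apply the same rule to the continuous secondary endpoints, and to the logistic model if it uses the emollient term. Report emollient hand-out by arm descriptively. The variable may stay in the imputation models as an auxiliary.

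The Results section says that enrolment is complete and analysis is under way, so timing matters. If the planned model has already been run, report the baseline-only ANCOVA beside it and label the emollient-adjusted model exploratory.

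No stated figure changes, no further data are needed, and power for the primary comparison stays at about 84%. The cost is a documented and dated change to a prespecified sensitivity model.
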